### Ethics approval and informed consent

The study protocol was approved by the Ethics Committee of Wuhan Union Hospital (approval number: 0407-2023) and will be approved by all participating centers. All procedures will be conducted in accordance with the principles of the Declaration of Helsinki. Written informed consent will be obtained from all patients or their legally authorized representatives prior to enrollment. Participation is entirely voluntary, and patient confidentiality will be strictly maintained throughout the study. Patients or their legally authorized representatives retain the right to withdraw from the study at any time and for any reason, without any impact on their subsequent medical care.

### Dissemination

Research data may only be disclosed or presented with the prior approval of the principal investigator. Study findings will be published in peer-reviewed journals and disseminated to the public.

## Discussion

This protocol outlines a phase III, randomized, single-blind, parallel, positive-controlled clinical trial designed to evaluate the effectiveness and safety of nalbuphine hydrochloride for analgesia in mechanically ventilated ICU patients. The study is particularly meaningful as it reflects a growing emphasis on individualized and safer analgesia strategies in critical care. If nalbuphine hydrochloride demonstrates analgesic efficacy comparable to hydromorphone hydrochloride while offering a more favorable safety profile, it can provide clinicians with an important alternative to ICU analgesia. Such results could help reduce reliance on deep sedation and limit risks associated with prolonged exposure to full μ-agonist opioids. While the design of this study incorporates several notable strengths, it also has inherent limitations.

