Indeed, although traditional opioids remain mainstays of analgesic therapy in the ICU, they are associated with notable adverse effects. Dose-dependent respiratory depression poses ongoing risks even in mechanically ventilated patients, suppression of gastrointestinal motility may delay recovery, and growing evidence links their use to long-term dependence and increased cumulative opioid exposure (Devlin et al., 2018; Müller-Lissner et al., 2017; Donohue et al., 2019). These drawbacks highlight the need for viable therapeutic alternatives. Nalbuphine may offer a favorable safety profile in ICU patients due to the above advantages. However, high-quality clinical data supporting its use specifically in ICU patients remain limited. Critical illness frequently alters drug absorption, distribution, metabolism, and excretion (Chen and Huang, 2024), and analgesic requirements in this population may differ significantly from those observed in surgical or obstetric cohorts, thus necessitating targeted evaluation. To address these evidence gaps, we conduct a clinical study to evaluate the efficacy and safety of nalbuphine hydrochloride for analgesia in ICU patients. To rigorously evaluate its role, hydromorphone hydrochloride, a potent μ-opioid agonist widely used in critical care analgesia (Liu and Gropper, 2003), was selected as the positive control to determine whether nalbuphine can provide non-inferior analgesia while reducing the adverse effects commonly associated with traditional opioids. Collectively, our study provides essential evidence for nalbuphine’s potential role in critical care analgesia.

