### Estimation of sample size

The sample size estimation is based on a non-inferiority design. According to previous findings and literature reports (Liu et al., 2018), nalbuphine is capable of maintaining the target analgesic effect within 3–24 h post-administration, with CPOT scores ≤2 for more than 70% of the time. An analgesic success rate approaching 100% is anticipated. We estimate an efficacy of 99% in the experimental group, and the control groups. Following consultation of several experts, the non-inferiority margin δ is set at −8%, meaning that an 8% reduction in efficacy representing the maximum clinically acceptable difference. A two-sided significance level of α = 0.05 and a power of 80% (β = 0.2) are applied. Sample size estimation is conducted using the Farrington and Manning method via PASS 2022 software, assuming a 1:1 allocation ratio between the two groups, and 73 participants per group is required. Assuming an anticipated dropout rate of approximately 12%, a total of 168 subjects is needed.

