### Statistical analysis

Statistical analyses will be performed using SAS software (version 9.4 or higher). Continuous variables will be presented as mean ± standard deviation for normally distributed data and median ± interquartile range for non-normally distributed data, whereas categorical variables will be summarized as frequencies and percentages. All statistical tests and confidence intervals (CI) will be two-sided, with statistical significance defined as a p-value less than 0.05. The difference in analgesic success rates between the experimental and control groups will be estimated using the Miettinen and Nurminen method to calculate the two-sided 95% CI. Non-inferiority will be established if the lower bound of this interval exceeds −8%. The proportion of time during which patients maintain a CPOT score ≤2 and a RASS score between −2 and +1 will be analyzed using the arcsine square root transformation, followed by between-group comparison via the t-test. Time from initiation of study drug to successful weaning and time to ICU discharge will be illustrated using Kaplan-Meier survival curves and compared using the log-rank test. The frequency and dosage of rescue propofol sedation, along with total propofol dose administered, will be compared between groups using either the t-test or Wilcoxon rank-sum test, depending on data distribution. The proportions of patients requiring concomitant propofol sedation, weaning success rate, and ICU discharge rate will be compared using the χ^2^ test or Fisher’s exact test. The incidence of adverse events will also be assessed using χ^2^ test or Fisher’s exact test.

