### Strengths

A major strength of this trial is its robust and pragmatic phase III design. This design ensures that the study is adequately powered to provide conclusive, real-world evidence on the efficacy and safety of nalbuphine hydrochloride in ICU patients. The randomized, parallel-group, positive-controlled methodology strongly enhances internal validity. Randomization minimizes selection bias and ensures comparable baseline characteristics between groups, thereby strengthening the causal inference between the intervention and the outcomes. The use of hydromorphone hydrochloride—rather than a placebo—is both ethically appropriate and clinically relevant for managing pain in critically ill patients. It enables direct comparison of nalbuphine’s performance against a current standard of care, which is the most meaningful question for clinicians. Another strength lies in the selection of the patient population and endpoints. ICU patients frequently experience complex and undertreated pain, representing a significant unmet clinical need (Puntillo et al., 2014). Use of validated tools such as the CPOT (Gélinas et al., 2006) ensures standardized and reliable pain assessment. Finally, nalbuphine’s low abuse potential has broader implications for public health. Its expanded use in ICU settings may support global efforts to reduce opioid misuse and dependence.

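### The Strengths section claims adequate power for safety as well as efficacy, but the only power calculation covers analgesic success, so the trial is not shown to be powered for safety

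*Protocol article*

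**What the plan says.** - **Introduction.** Hydromorphone was chosen as control to find out whether nalbuphine gives "non-inferior analgesia while reducing the adverse effects commonly associated with traditional opioids". Safety is therefore half of the stated question.
- **Discussion, opening paragraph.** The drug's clinical value is tied to comparable analgesia "while offering a more favorable safety profile". The sentence is conditional: it says what a favourable result would mean.
- **Strengths.** The design is said to make the study "adequately powered to provide conclusive, real-world evidence on the efficacy and safety of nalbuphine hydrochloride in ICU patients". This is an unconditional statement about power, and it names safety.
- **Estimation of sample size.** "The sample size estimation is based on a non-inferiority design". The inputs are the primary outcome only: "We estimate an efficacy of 99% in the experimental group, and the control groups", a margin of −8%, and "A two-sided significance level of α = 0.05 and a power of 80% (β = 0.2) are applied". The result is 73 per group, raised to 168 in total for about 12% dropout. No safety quantity appears.
- **Statistical analysis.** "The incidence of adverse events will also be assessed using χ^2^ test or Fisher’s exact test", with all tests two-sided at 0.05.
- **Limitations.** The section covers the analgesic ceiling, dose equivalence, generalizability, single-blind assessment and the short treatment period. It does not mention limited power for adverse events, so nothing later in the article corrects the Strengths sentence.

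**The concern.** Power belongs to a specified comparison with specified rates. The article specifies these for analgesic success and for nothing else, yet claims adequate power and conclusive evidence for safety too.

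The consequence lies in how the results may be read. A reader who accepts that safety was adequately powered has reason to take a non-significant adverse-event test as showing similar safety. With moderate event rates such a result would be likely even if nalbuphine truly halved the rate. The second half of the Introduction's question would then seem to have been answered when it had not been.

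**Working it through.** **1. Reproduce the plan's own figure.** Inputs from Estimation of sample size: success 99% in both groups, margin −0.08, two-sided α 0.05 (one-sided 0.025 for non-inferiority), power 80%, Farrington and Manning method.

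- Restricted estimates under a true difference of −0.08: 0.9149 (nalbuphine) and 0.9949 (hydromorphone).
- Null SD term: √(0.9149×0.0851 + 0.9949×0.0051) = 0.288.
- Alternative SD term: √(2×0.99×0.01) = 0.1407.
- n per group = [(1.960×0.288 + 0.8416×0.1407) / 0.08]² = 72.86, so 73.

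This matches the stated 73. Allowing for dropout, 73/0.88 = 82.95, or 83 per group and 166 in total. The stated 168 (84 per group) agrees with a rate given as approximate. The efficacy inputs alone account for the size, so no safety consideration entered it.

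**2. Power of that size for an adverse event.** The documents give no adverse-event rates, so every control rate below is an assumption. The effect examined is a halving. Power is the exact sum, over all pairs of event counts (x, y), of Bin(x; n, p_C) × Bin(y; n, p_C/2) wherever the Pearson chi-square exceeds its 5% critical value. The two columns are the evaluable number (73) and the full randomised number (84).

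| Assumed control rate | Nalbuphine rate | Power, 73 per arm | Power, 84 per arm |
|---|---|---|---|
| 5% | 2.5% | 11% | 12% |
| 10% | 5% | 21% | 22% |
| 20% | 10% | 40% | 44% |
| 30% | 15% | 59% | 66% |
| 40% | 20% | 76% | 82% |
| 50% | 25% | 89% | 92% |

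Fisher's exact test, which the plan also allows, gives less at 84 per arm: 15% (10% to 5%), 37% (20% to 10%), 58% (30% to 15%) and 77% (40% to 20%).

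**3. Reduction needed for 80% power (exact chi-square).** A 20% control rate would have to fall to 5.2% with 73 per arm or 5.9% with 84. A 10% rate would have to fall below 1%.

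**4. Size needed for a halving.** n per arm = [1.960·√(2p̄(1−p̄)) + 0.8416·√(p₁(1−p₁) + p₂(1−p₂))]² / (p₁−p₂)².

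- 20% to 10%: [1.960×0.5050 + 0.8416×0.5000]² / 0.01 = 199 per arm.
- 10% to 5%: [1.960×0.3725 + 0.8416×0.3708]² / 0.0025 = 435 per arm.

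**5. Rare events.** If none of 84 patients has a given event, the upper limit of the two-sided 95% interval is 1 − 0.025^(1/84) = 4.3%.

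**The case against.** The strongest reply is that a reader might infer that the trial cannot detect any plausible safety difference, and that this goes too far. It does. With no event rates in the documents, nothing shows that the relevant rate is low. The plan tests the incidence of adverse events, which on its wording can include the overall incidence, and that could be 40% or more. A halving from 40% has 76% / 82% power and from 50% has 89% / 92%. What can be said is that the trial is not shown to be powered for safety, not that it is blind to every difference.

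Other parts of the reply also stand:

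- The conditional sentence opening the Discussion and the aim in the Introduction are not errors. A trial may study safety without being sized for it. The misstatement is in Strengths.
- Nothing is miscalculated, since 73 per group reproduces. A reader might infer that the sample size is wrong, but the documents do not support that.
- Safety reporting is not limited to p-values. Categorical data are summarised as frequencies and percentages, and severity, timing, outcome and relationship to study drug are recorded.
- Confidence intervals for adverse-event differences may be specified in an analysis plan not shown here, so their absence from the article is no fault.
- No claim of equivalent safety is planned. Misreading a non-significant test is a risk created by the Strengths wording, not a stated intention.

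None of this rescues the Strengths sentence. A separate analysis plan could add safety analyses, but it would not make the stated calculation one for safety.

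**Conclusion.** The concern holds as a misstated power property. The article claims adequate power for conclusive safety evidence, its one power calculation concerns analgesic success, and its limitations do not correct the claim.

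The size of the gap rests on assumed control rates and on a halving as the effect of interest. Chi-square power runs from 11% / 12% at a 5% control rate to 59% / 66% at 30% (73 / 84 per arm), and reaches 80% only for large reductions in common events. At 84 per arm a true halving from 20% would be missed 56% of the time (1 − 0.444). The primary comparison, its margin and its sample size are not called into question by this point.

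**What to change.** In Strengths, restrict the claim of adequate power to the primary non-inferiority comparison of analgesic success. State there that the adverse-event comparison is descriptive or exploratory, and that a non-significant adverse-event test is not evidence of comparable safety.

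Preferably, also report adverse-event risk differences with 95% confidence intervals beside the tests named in Statistical analysis. This is secondary to correcting the claim.

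The cost is a few sentences, extra columns in the safety tables if the intervals are added, and a less favourable stated property. Sample size and trial conduct do not change.

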### Strengths

A major strength of this trial is its robust and pragmatic phase III design. This design ensures that the study is adequately powered to provide conclusive, real-world evidence on the efficacy and safety of nalbuphine hydrochloride in ICU patients. The randomized, parallel-group, positive-controlled methodology strongly enhances internal validity. Randomization minimizes selection bias and ensures comparable baseline characteristics between groups, thereby strengthening the causal inference between the intervention and the outcomes. The use of hydromorphone hydrochloride—rather than a placebo—is both ethically appropriate and clinically relevant for managing pain in critically ill patients. It enables direct comparison of nalbuphine’s performance against a current standard of care, which is the most meaningful question for clinicians. Another strength lies in the selection of the patient population and endpoints. ICU patients frequently experience complex and undertreated pain, representing a significant unmet clinical need (Puntillo et al., 2014). Use of validated tools such as the CPOT (Gélinas et al., 2006) ensures standardized and reliable pain assessment. Finally, nalbuphine’s low abuse potential has broader implications for public health. Its expanded use in ICU settings may support global efforts to reduce opioid misuse and dependence.

Beyond these methodological strengths, nalbuphine’s distinct pharmacological profile—as a selective κ-opioid receptor agonist and partial μ-opioid receptor antagonist—confers intrinsic opioid-sparing properties that are consistent with contemporary clinical imperatives to reduce cumulative opioid exposure in critically ill patients (Maciel et al., 2023). This mechanism may attenuate the incidence and severity of adverse effects associated with full μ-opioid agonists, including postoperative ileus, dose-dependent respiratory depression, and the development of analgesic tolerance. Furthermore, because the intervention protocol defines pain and sedation targets using validated, objective assessment instruments, it may be applicable across diverse ICU populations, including medical, surgical, and trauma patients. In specialized units—such as neurosurgical and cardiothoracic ICUs—nalbuphine’s favorable hemodynamic neutrality and minimal impact on level of consciousness may confer additional therapeutic advantages. Nevertheless, prespecified stratified analyses by primary admission diagnosis and ICU subspecialty will be critical to rigorously evaluate generalizability and inform context-specific implementation.

### Limitations

Despite these strengths, several limitations merit consideration. First, although nalbuphine exhibits a ceiling effect for analgesia, this occurs at doses exceeding 0.4 mg/kg, which are not reached in our protocol (maximum 10 mg loading plus 5 mg/h maintenance). Within the selected dose range, dose-dependent analgesic efficacy is preserved. Nevertheless, the ceiling effect may limit efficacy in patients with very high opioid requirements, which we have acknowledged as a study limitation. Second, one limitation of our study is the lack of precise equipotent dosing between nalbuphine and hydromorphone. The chosen dose ratio (approximately 4:1) may underestimate nalbuphine’s required dose if the true potency ratio is 5-7.5:1. To mitigate this, our protocol permits supplemental boluses and upward titration to a maximum of 5 mg/h. Moreover, we will conduct sensitivity analyses using alternative potency assumptions to assess the robustness of the non-inferiority conclusion. Future dose-optimization studies in ICU patients are warranted. Third, the protocol, as described, may face challenges related to generalizability. ICUs are highly heterogeneous (Zimmerman et al., 2006), and patient populations can vary significantly between centers in terms of primary diagnoses (e.g., medical, surgical, or trauma), severity of illness, and baseline organ function. If the inclusion and exclusion criteria are too restrictive, the results may not be applicable to all subtypes of critically ill patients. Additionally, the findings will be directly comparable only to the specific positive-control analgesic chosen, conclusions may not extend to all opioids or analgesics used in the ICU. The single-blind design carries an inherent risk of assessment bias despite mitigation strategies, and the exclusion of patients with severe organ dysfunction, hemodynamic instability, or need for deep sedation further limits generalizability to the sickest ICU subpopulations. Variability in patient pharmacodynamics—especially in those with organ dysfunction, comorbidities, or concurrent sedative use—may also influence analgesic response. Moreover, the 24-h intervention period may not capture longer-term outcomes such as delirium, opioid withdrawal, or post-ICU dependence, and variations in institutional sedation protocols and nursing expertise could influence implementation fidelity across centers. These factors should be considered when interpreting results and may inform future research aimed at optimizing dosing strategies or evaluating specific subgroups.

To maximize clinical utility, prespecified subgroup and sensitivity analyses are necessary. Subgroup analyses stratified by baseline hepatic function (e.g., Child-Pugh class) and renal function (e.g., KDIGO stage) would assess whether nalbuphine’s noninferiority is maintained across the spectrum of organ dysfunction severity. Sensitivity analyses adjusting for key potential confounders—including illness severity (e.g., APACHE II score), concomitant sedative use, and delirium status—would further enhance the robustness and generalizability of the primary findings. Although these analyses are exploratory, they are valuable for generating new research ideas and guiding personalized pain management in critically ill patients.

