### Outcomes

The primary outcome is the analgesic success rate during 24 h of study drug administration. Analgesic success is defined as the fulfillment of both criteria: 1) no administration of rescue analgesic medication, and 2) maintenance of a CPOT score ≤2 for at least 70% of the observation period during study drug infusion.

The secondary outcomes include: 1) The percentage of time within CPOT score ≤2 and RASS score between −2 and +1 during 24 h of study drug administration: This metric represents the proportion of time during which a patient maintains a CPOT score of ≤2 and a RASS score between −2 and +1, relative to the total duration of study drug administration. 2) The frequency and dosage of rescue sedation during 24 h of study drug administration: The frequency refers to the number of rescue sedative administrations, while the dosage indicates the total amount of propofol administered as rescue sedation during the infusion of the study drug. 3) The proportion of patients requiring rescue sedation during 24 h of study drug administration: This is the percentage of patients in each treatment group who received concomitant propofol for rescue sedation during study drug infusion, calculated as (Number of patients receiving propofol/Total number of patients in the group) × 100%. 4) The total cumulative dose of rescue sedative during 24 h of study drug administration: The sum of all propofol doses administered as rescue sedation during the period of study drug infusion. 5) The time to successful weaning and ICU discharge during 24 h of study drug administration: Time to successful weaning is defined as the interval from the initiation of the study drug to liberation from mechanical ventilation. Time to ICU discharge is defined as the interval from study drug initiation to actual ICU discharge. Successful weaning is achieved when the patient is extubated and subsequently maintains stable spontaneous breathing without the need for reintubation. 6) The weaning success rate and the proportion of patients discharged from the ICU: The weaning success rate reflects the percentage of patients successfully weaned from mechanical ventilation. The proportion of patients discharged from the ICU indicates the percentage of patients transferred out of the ICU within the observation period.

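### The promised potency sensitivity analyses do not act on the stated non-inferiority comparison, which contains no dose or potency term

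*Protocol article*

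**What the plan says.** In the protocol article, Discussion, Limitations, unequal potency is the second limitation listed: "The chosen dose ratio (approximately 4:1) may underestimate nalbuphine’s required dose if the true potency ratio is 5-7.5:1". Supplemental boluses and upward titration are named as mitigation. The article then adds a commitment: "we will conduct sensitivity analyses using alternative potency assumptions to assess the robustness of the non-inferiority conclusion".

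The conclusion to be tested is fixed elsewhere in the article:

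- **Outcomes.** Success requires both "no administration of rescue analgesic medication" and "maintenance of a CPOT score ≤2 for at least 70% of the observation period during study drug infusion".
- **Statistical analysis.** The difference in success rates "will be estimated using the Miettinen and Nurminen method to calculate the two-sided 95% CI", and "Non-inferiority will be established if the lower bound of this interval exceeds −8" percent.
- **Estimation of sample size.** The same margin is used ("the non-inferiority margin δ is set at −8" percent), with 99% success assumed in both groups.
- **Intervention.** Both drugs are titrated on CPOT and RASS. Propofol, labelled rescue sedation, is started when CPOT stays above 2 at 3.0 mg/h nalbuphine or 2.0 mg/h hydromorphone.

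**The concern.** A sensitivity analysis tests a conclusion only if the varied assumption enters the result or the inference drawn from it. Here the potency ratio is to be varied, but neither the endpoint, the estimator, the margin nor the decision rule uses a dose or a ratio.

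The risk lies in the reporting. An unchanged result at 5:1 or 7.5:1 could be presented as evidence of robustness when nothing was tested. If a ratio were instead forced into a regression on dose, the result could move for reasons unrelated to non-inferiority. Either way, a limitation that the article itself raises would appear to have a safeguard that does not work.

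**Working it through.** **1. The plan's own sample size, and whether potency enters it.** Inputs from Estimation of sample size: 99% in both groups, δ = −0.08, two-sided α = 0.05 (one-sided 0.025), power 80%, 1:1, Farrington-Manning.

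n per group = [(z₀.₉₇₅·s₀ + z₀.₈₀·s₁) / (p₁ − p₂ − δ)]²

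- Restricted estimates under the null: 0.9149 and 0.9949, so s₀ = √(0.9149×0.0851 + 0.9949×0.0051) = 0.2880.
- s₁ = √(2×0.99×0.01) = 0.1407.
- n = [(1.960×0.2880 + 0.8416×0.1407) / 0.08]² = 72.86, so 73 per group, as stated.

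No dose or ratio is an input.

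**2. The primary interval.** The Miettinen-Nurminen lower limit is the value d that solves

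(p̂₁ − p̂₂ − d) / √{[q₁(1−q₁) + q₂(1−q₂)]/n × 2n/(2n−1)} = 1.96,

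where q₁ and q₂ are the restricted estimates with q₁ − q₂ = d. Its only inputs are the two success counts and the group size. Example counts with n = 73 (chosen for illustration):

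| Successes, nalbuphine vs hydromorphone | Lower limit | Against −8% | At 4:1, 5:1, 7.5:1 |
|---|---|---|---|
| 72 vs 72 | −6.2% | non-inferior | identical |
| 71 vs 72 | −8.3% | not shown | identical |

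One patient's outcome changes the verdict. The assumed ratio cannot, because no patient's success status depends on it.

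**3. The alternative: putting converted dose into a model.** Under Intervention, dose responds to CPOT after randomisation, and CPOT is half of the endpoint. Adjusting for it conditions on a consequence of treatment and of pain severity. A simulation shows the hazard. All its settings are assumptions, not trial figures:

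- 200,000 patients per arm, with the same standard normal pain score x in both arms.
- True success the same in both arms, logit = 4.5 − 1.2x (about 98% overall).
- Rates titrated to pain in 0.5 mg/h steps: nalbuphine 2.5 + 1.0x, held within 1–5 mg/h; hydromorphone 1.0 + 0.7x, held within 0.5–3 mg/h.
- Linear model of success on arm and hydromorphone-equivalent dose.

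| Assumed ratio | Unadjusted difference (points) | Adjusted difference (points) |
|---|---|---|
| 4:1 | 0.0 | −2.3 |
| 5:1 | 0.0 | −3.0 |
| 7.5:1 | 0.0 | −3.7 |

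The true difference is nil, yet the adjusted one grows with the assumed ratio. That is an artefact of conditioning on titrated dose.

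**4. The stated ratio against the dosing rules.** From Intervention:

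| Point in the regimen | Nalbuphine / hydromorphone (mg/h) | Ratio |
|---|---|---|
| Starting rate | 2.0 / 0.5 | 4:1 |
| Lower end of range | 1.0 / 0.5 | 2:1 |
| Upper end of range | 5.0 / 3.0 | 1.67:1 |
| Propofol trigger | 3.0 / 2.0 | 1.5:1 |

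The approximate 4:1 in Limitations matches only the starting rates.

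**5. Where under-dosing could be hidden.** Under-dosing that leaves CPOT above 2 counts against nalbuphine through the CPOT criterion. Propofol started for CPOT >2 is called rescue sedation, so read literally it does not breach the rescue-analgesic criterion. A patient whose score falls once propofol is running may still count as a success.

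**The case against.** The strongest reply is that the sentence sits in a Discussion, names no method, and condenses a fuller document in which a dose-response model may be defined. Part of this stands. It cannot be said that every potency-based analysis would return the same number; step 3 shows that one would not. Exact invariance holds only for the stated primary comparison. But the point is not missing detail. The article assigns the analysis a purpose, testing the non-inferiority conclusion, that neither relabelled doses nor adjustment for titrated dose can serve.

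A reader might also infer more than the documents support:

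- **That unequal potency is the main threat and is declared dealt with.** The article lists it among several limitations, says the ratio may be too low, and calls for later dose-optimisation studies.
- **That under-dosing endangers a positive result generally.** Under-dosed nalbuphine would tend to lose time at CPOT ≤2, which works against showing non-inferiority. Titration in both arms also absorbs part of a wrong starting ratio. The route to false reassurance is the narrower one in step 5.
- **That counting propofol as failure would shift the result by a known amount.** The documents give no rescue rates, so any such figure would be invented.

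It is also fair to say that counting propofol as failure does not test potency. At the triggers, 3.0 mg/h nalbuphine converts to 3.0/4 = 0.75, 3.0/5 = 0.6 or 3.0/7.5 = 0.4 mg/h hydromorphone-equivalent, against 2.0 mg/h in the control arm. The failure rule therefore carries the same inequality. Propofol use is, besides, already compared between arms as a secondary outcome. What that comparison lacks is a judgement against the −8% margin.

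**Conclusion.** The concern holds in a limited form. The promised potency analyses are not a valid robustness test of the stated non-inferiority comparison: relabelling doses at 5:1 or 7.5:1 leaves that result unchanged, and adjusting for converted dose conditions on a post-randomisation variable driven by CPOT. The first part follows from the definitions and needs no assumption. The second rests on the titration rule; the simulated differences only illustrate it.

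The primary estimate, margin, sample size and decision rule are unaffected. No numerical effect on the trial's result is claimed. The point should be corrected before reporting, because the article promises a check that cannot do what is said of it, while a useful one is available from data the article says are collected.

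**What to change.** 1. In Limitations, withdraw the statement that alternative potency assumptions test the non-inferiority conclusion. Keep unequal potency as a limit on interpretation.
2. Prespecify a supplementary Miettinen-Nurminen comparison against −8% in which propofol started for CPOT >2 counts as failure, in addition to the existing success criteria.
3. Add a by-arm table of infusion rates reached and study-drug doses given.
4. Describe item 2 as a check on whether propofol masks inadequate analgesia. State that it is not potency-neutral, since the triggers differ by arm (3.0 versus 2.0 mg/h, 1.5:1).
5. Reconcile the approximate 4:1 in Limitations with the rates in Intervention, where it matches only the starting rates. This review takes no position on which dosing is right.

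Cost: a reworded passage, one extra analysis and one table. Table 1 already schedules recording of study-drug and rescue-sedative doses, and Data collection and management has CPOT documented before each dose adjustment. The downside is that the supplementary analysis may not support non-inferiority. If the sponsor declines item 2, items 1 and 3 alone still remove the unsupported claim.
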